During an initial phone contact, a CHWS staff member will complete a screening demographic questionnaire with the carer to ensure they meet the study inclusion criteria. Once eligibility and interest in participation in the study are determined, the carer will be asked to review the explanatory statement and consent form, and if willing to participate in the research, to sign the consent form and return it to the CHWS staff. CHWS staff will then inform the research team of carers who have agreed to participate in the research. Involvement in the research study will include allowing data from baseline and 6 month follow-up assessments to be used to evaluate the service outcomes and possibly being asked to be involved in a semi-structured interview after the 6 month assessment (which will involve a separate explanatory and consent form). Participants will be purposefully sampled for these interviews, aiming for diversity of age, years in the carer role, nature of prioritised needs, and health status of the carer. Carers who would like to find out more about the study before consenting to participate will be able to follow up with the CHWS staff member, or members of the research team.

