A purposeful sample of approximately 15–25 carers completing the 6 month assessment will also be asked if they are willing to participate in a semi-structured interview (estimated duration 45 minutes). The sample size for interviews will be determined by data saturation. Interviews will be conducted by an experienced qualitative researcher face-to-face or online, dependent upon the preference of the carer, and will be recorded to ensure the accuracy of reporting and analysis. The interviews will explore in more depth the questions in the CHWS satisfaction survey, as well as seek perspectives about recommendations on how the CHWS could be improved. Carers who participate in the interviews will be provided with a $AUD50 gift card as an acknowledgement of their time contribution.

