#### CHWS staff (n = 4).

Staff working at the CHWS within the last six months of the evaluation of the CHWS will be sent a letter (via email) by a member of the research team, inviting them to participate in the evaluation of the CHWS. Consenting staff will be involved in a semi-structured interview (approx. 30–45 minutes) focused on their perspectives about, and their acceptability of the Service over the previous 18 months. Location/mode and timing of the interview will be determined in discussion with consenting staff and can be conducted during their funded work time with the CHWS. Interviews will be conducted by an experienced qualitative researcher and will be recorded to ensure the accuracy of reporting and analysis. If any staff leave the CHWS during the two-year evaluation, they will be asked to undertake an exit interview (similar questions as described above).

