#### Implementation (service-related) outcomes.

As well as the carer-related outcomes detailed and in Table 1, the research team will also be evaluating **implementation outcomes** for the CHWS (how well the CHWS succeeds in meeting key service-related implementation outcomes). These will be based on the RE-AIM framework (components are Reach, Effectiveness, Adoption, Implementation, and Maintenance) [59]. Primary implementation outcomes are reach (outlined below) and adoption (% completing intervention and 6 month assessments).

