a)*Reach* will be determined through referrals received, aiming for >80% of appointment slots for all CHWS staff being utilised in the last six months of the study recruitment period; and overall sample size relative to the planned sample size (see analysis and sample size calculation section). Sources of referrals (medical practitioners, allied health professionals, carers themselves) will be reported;b)*Effectiveness* outcomes will mainly include the carer outcome measures (Table 1), and also a *cost-effectiveness* evaluation. A cost-utility analysis will be conducted using a societal perspective over a 12 month time horizon (6 months before the carer’s first appointment and 6 months following the carer’s first appointment). Cost data will include CHWS intervention costs (excluding research costs); carer emergency department presentations and hospital admissions (self-report); the quantity of care provided to the person requiring care, including average weekly hours of care provided by the carer, by other people who are not paid, and by other people who are paid (self-report). In addition, the carer will report the “preferred” and “actual” weekly hours spent on their top three leisure activities (noting when the carer role contributes to the gap between “preferred” and “actual” hours of participation). Effect data will be based on the utility index derived from the EQ-5D-5L [37], measured during the carer’s initial appointment and again at their 6 month follow-up assessment. The change in utility index between initial assessment and 6 months will be used to determine quality-adjusted life years (QALYs) gained or lost by the carer. Cost and effect data will be combined to determine incremental cost-effectiveness ratio (ICER) per QALY gained, with a threshold of <$AUD50,000/QALY gained to determine cost-effectiveness [55].c)*Adoption* will be evaluated through several service system outcomes (percentage completing intervention programs and 6 month assessment, number of interventions undertaken, and number of intervention sessions undertaken with CHWS staff). Acceptability of the service will be evaluated through the CAQ-8 and associated survey items, and interviews of a purposive sampling of carers (after the 6 month assessment), service referrers, and an interview with consenting CHWS staff in the last six months of the intervention, or an exit interview for staff leaving the service;d)*Implementation* includes fidelity of the program as intended (which will be evaluated by members of the research team reviewing 5% of de-identified patients’ assessments and intervention programs implemented against CHWS protocol) and adaptations (CHWS staff will document issues and adaptations made during the CHWS implementation and report these to the research team; and will be asked to comment on adaptations in the staff interviews). Other service-related aspects of implementation will be captured as part of the economic evaluation (e.g., costs, non-attendance at booked sessions);e)*Maintenance* at the individual (carer) level will be evaluated through the proportion of carers completing the 6 month assessment and completing interventions. At the system level, maintenance will be determined through the CHWS being able to continue beyond its initial two year intervention period.

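### Carer interviews are drawn only from carers who complete the 6 month assessment, so those who count against adoption by missing it have no planned interview route to explain why

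*Protocol article*

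**What the plan says.** The sampling rule for carer interviews is in the protocol article under Procedure: Service screening and assessment tools: "A purposeful sample of approximately 15–25 carers completing the 6 month assessment will also be asked if they are willing to participate". The Carers subsection of Participants and recruitment describes the same interview in the consent information, as "possibly being asked to be involved in a semi-structured interview after the 6 month assessment". It lists the aims of the purposeful sampling as "aiming for diversity of age, years in the carer role, nature of prioritised needs, and health status of the carer". Whether the carer completed or withdrew is not on that list.

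The subsection on implementation outcomes names "adoption (% completing intervention and 6 month assessments") as a primary implementation outcome alongside reach. Under the Adoption item it gives the sources on acceptability as the satisfaction questionnaire with its survey items, and "interviews of a purposive sampling of carers (after the 6 month assessment), service referrers, and an interview with consenting CHWS staff". For staff who leave, the CHWS staff subsection adds: "If any staff leave the CHWS during the two-year evaluation, they will be asked to undertake an exit interview". The article describes no exit or withdrawal interview for carers.

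**The concern.** Acceptability to carers is one of the study's stated aims, and the interviews are the in-depth source on it. Their sampling frame depends on an event that forms part of the adoption outcome. A carer who does not complete the 6 month assessment is counted against adoption and is also outside the group that can be interviewed.

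Carers who found the service hard to use, poorly timed or unhelpful are plausibly over-represented among those who miss the assessment. If so, the interview themes will lean towards the views of carers who stayed in contact. The findings are meant to inform scaling up, and barriers that made carers drop away are among the most useful things an evaluation could report for that purpose.

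**Working it through.** The plan states no figure on this point, so there is nothing to reproduce. The check sets the relevant passages side by side and adds simple arithmetic for scale.

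**1. Who can be interviewed.** The sampling rule in the Procedure section limits the frame to carers completing the 6 month assessment. The Carers subsection and the Adoption item both place the interview after that assessment. The three places agree. Data analysis continues carer interviews to saturation but does not widen the frame, and saturation can be reached among completers without hearing from anyone else.

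**2. What the interviews inform.** They are listed under Adoption as evidence on acceptability. Adoption is measured by completion of the intervention and of the 6 month assessment. The frame is therefore selected on part of the outcome that the interviews help to explain.

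**3. Who is outside the frame.** The article describes several ways in which a carer may finish or stop:

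| Carer's course | Within the interview frame? |
|---|---|
| Completes intervention and 6 month assessment | Yes |
| Stops the intervention but attends the 6 month assessment | Yes |
| Needs met early, final assessment brought forward | Yes, on a natural reading |
| Ceases after the care recipient dies or enters permanent residential care | Re-assessment offered if acceptable to the carer; interview not mentioned |
| Stops or loses contact and is not assessed | No |

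The excluded group is thus carers who do not complete the assessment. It is narrower than all carers who leave the service. The early finishers whom the plan expressly keeps in view are those whose needs were met.

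**4. Other sources on the excluded group.**
- The CSQ-8 and additional satisfaction items, some of them open-ended, are planned for all carers. The article does not say when they are given or how they reach a carer who has left.
- Staff and referrers are also interviewed on acceptability, but on a carer's reasons for leaving they are second-hand. Referrers qualify only with two or more referrals.

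**5. Scale.** The article gives no non-completion rate, so a range is assumed. Carers outside the frame = 137 × assumed rate:
- 10%: 137 × 0.10 = 13.7, about 14
- 20%: 137 × 0.20 = 27.4, about 27
- 30%: 137 × 0.30 = 41.1, about 41
- 40%: 137 × 0.40 = 54.8, about 55

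The 15–25 interviewees would be 15/137 = 11% to 25/137 = 18% of the carer sample, all of them completers.

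**6. What a few reserved interviews could add (illustration only).** Suppose a reason for leaving is held by a proportion p of non-completers, and five of them are interviewed as if drawn independently. The chance that at least one holds it is 1 − (1 − p)^5:
- p = 0.30: 1 − 0.7^5 = 0.83
- p = 0.40: 1 − 0.6^5 = 0.92
- p = 0.50: 1 − 0.5^5 = 0.97

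The values of p are assumed. Purposeful sampling is not random, and five non-completers would have to agree. The figures show only that a small number of interviews can be informative.

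**The case against.** The strongest reply is that the plan already has several routes to acceptability and that nothing in it is misstated or contradictory. The questionnaire and open-ended items are meant for every carer and ask what did and did not work well. The interviews explore the same topics in more depth. Staff and referrers are interviewed too. Completing the assessment is not the same as staying with the service, so some carers who stopped sessions can still be interviewed. How withdrawal reasons are recorded may be in a fuller protocol that is not shown. Late contact is also difficult: recruitment closes on 31 May 2025 and the project ends in December 2025, so some early leavers would be approached long after they left.

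Much of this stands, and it limits the point. A reader might infer that every carer who leaves is barred from interview, that carer interviews are the only interview source on acceptability, or that the study cannot learn why carers left. The documents support none of these. Carers who stop but are assessed remain eligible, two other groups are interviewed, and survey free text or staff accounts may reveal reasons.

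One part of the reply does not stand. The restriction to completers is a stated sampling rule, so it is not a detail left out by condensation. The survey could close part of the gap, but the article does not say how it reaches carers who leave. The plan recognises the value of hearing from leavers in the case of staff, with "or an exit interview for staff leaving the service", and offers carers no counterpart.

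**Conclusion.** The point holds for the carer interviews. Carers who do not complete the 6 month assessment count against a primary implementation outcome and have no planned interview route to explain why. The expected consequence is that carer interview themes tend to be favourable. This rests on the assumption that non-completers hold less favourable views on average, which is plausible but is not shown in the article.

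The size of the excluded group is unknown. The 14 to 55 carers above depend entirely on the assumed 10% to 40%, and the 83% to 97% is illustrative and should not be read as an estimate. The calculation of the adoption percentage, the sample size and the primary effectiveness analysis are not affected. This is an inexpensive improvement to the qualitative component and does not threaten the study's main result.

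**What to change.** - In the Procedure section, draw the purposeful sample from all consenting carers. Adjust the timing wording in the Carers subsection and in the Adoption item, which now reads "interviews of a purposive sampling of carers (after the 6 month assessment").
- Add completion status to the diversity criteria in the Carers subsection.
- Aim to hold about 5 of the existing 15–25 interviews for carers who stopped early or missed the 6 month assessment.
- Offer the CSQ-8 and the open-ended items when a carer stops, and say how they will be delivered.
- Report non-completers' themes separately. If few agree to be interviewed, report that uptake as a limitation.

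The total number of interviews does not change, and interviews already use a separate consent form. The costs are a minor ethics amendment, lower uptake among carers who have left, and fewer completer interviews: 15 − 5 = 10 to 25 − 5 = 20 if all five places are filled.

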#### CHWS staff (n = 4).

Staff working at the CHWS within the last six months of the evaluation of the CHWS will be sent a letter (via email) by a member of the research team, inviting them to participate in the evaluation of the CHWS. Consenting staff will be involved in a semi-structured interview (approx. 30–45 minutes) focused on their perspectives about, and their acceptability of the Service over the previous 18 months. Location/mode and timing of the interview will be determined in discussion with consenting staff and can be conducted during their funded work time with the CHWS. Interviews will be conducted by an experienced qualitative researcher and will be recorded to ensure the accuracy of reporting and analysis. If any staff leave the CHWS during the two-year evaluation, they will be asked to undertake an exit interview (similar questions as described above).

#### Referrers to the CHWS (n=20–25).

A purposeful sample of referrers to the CHWS who provided two or more referrals to the CHWS will be sent a letter from the CHWS manager (via email), inviting them to participate in the evaluation of the CHWS, together with an explanatory statement and consent form. Purposeful sampling will aim to achieve diversity in the disciplines of referrers (e.g., general practitioners, and allied health professionals). Referrers interested in participating will be able to contact the research team to complete their consent to participate. Consenting referrers will undertake a semi-structured interview (approx. 30 minutes) focused on their perspectives about, and their acceptability of, the CHWS based on their knowledge and interactions with the service, and the clients they referred to the CHWS. The location/mode and timing of the interview will be determined in discussion with consenting referrers. The sample size of referrers will be determined by data saturation. As an acknowledgment of their time, referrers will be provided with a $AUD50 gift card. Interviews will be conducted by an experienced qualitative researcher and will be recorded to ensure the accuracy of reporting and analysis.

#### Implementation (service-related) outcomes.

As well as the carer-related outcomes detailed and in Table 1, the research team will also be evaluating **implementation outcomes** for the CHWS (how well the CHWS succeeds in meeting key service-related implementation outcomes). These will be based on the RE-AIM framework (components are Reach, Effectiveness, Adoption, Implementation, and Maintenance) [59]. Primary implementation outcomes are reach (outlined below) and adoption (% completing intervention and 6 month assessments).

a)*Reach* will be determined through referrals received, aiming for >80% of appointment slots for all CHWS staff being utilised in the last six months of the study recruitment period; and overall sample size relative to the planned sample size (see analysis and sample size calculation section). Sources of referrals (medical practitioners, allied health professionals, carers themselves) will be reported;b)*Effectiveness* outcomes will mainly include the carer outcome measures (Table 1), and also a *cost-effectiveness* evaluation. A cost-utility analysis will be conducted using a societal perspective over a 12 month time horizon (6 months before the carer’s first appointment and 6 months following the carer’s first appointment). Cost data will include CHWS intervention costs (excluding research costs); carer emergency department presentations and hospital admissions (self-report); the quantity of care provided to the person requiring care, including average weekly hours of care provided by the carer, by other people who are not paid, and by other people who are paid (self-report). In addition, the carer will report the “preferred” and “actual” weekly hours spent on their top three leisure activities (noting when the carer role contributes to the gap between “preferred” and “actual” hours of participation). Effect data will be based on the utility index derived from the EQ-5D-5L [37], measured during the carer’s initial appointment and again at their 6 month follow-up assessment. The change in utility index between initial assessment and 6 months will be used to determine quality-adjusted life years (QALYs) gained or lost by the carer. Cost and effect data will be combined to determine incremental cost-effectiveness ratio (ICER) per QALY gained, with a threshold of <$AUD50,000/QALY gained to determine cost-effectiveness [55].c)*Adoption* will be evaluated through several service system outcomes (percentage completing intervention programs and 6 month assessment, number of interventions undertaken, and number of intervention sessions undertaken with CHWS staff). Acceptability of the service will be evaluated through the CAQ-8 and associated survey items, and interviews of a purposive sampling of carers (after the 6 month assessment), service referrers, and an interview with consenting CHWS staff in the last six months of the intervention, or an exit interview for staff leaving the service;d)*Implementation* includes fidelity of the program as intended (which will be evaluated by members of the research team reviewing 5% of de-identified patients’ assessments and intervention programs implemented against CHWS protocol) and adaptations (CHWS staff will document issues and adaptations made during the CHWS implementation and report these to the research team; and will be asked to comment on adaptations in the staff interviews). Other service-related aspects of implementation will be captured as part of the economic evaluation (e.g., costs, non-attendance at booked sessions);e)*Maintenance* at the individual (carer) level will be evaluated through the proportion of carers completing the 6 month assessment and completing interventions. At the system level, maintenance will be determined through the CHWS being able to continue beyond its initial two year intervention period.

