## Methods

A mixed methods one-group pre-post (6-month) study design will be utilised, using both quantitative and qualitative data. The protocol follows the checklist and guidelines described in the SPIRIT guidelines for the content of clinical trial protocols (Fig 1, and Supporting Information S1 Checklist) [29] and the ‘Template for Intervention Description and Replication (TIDieR) (Supporting Information, S2 Checklist) [30]. The project commenced recruitment on March 1 2024, recruitment will end on 31 May 2025, and the project will end in December 2025. The study was retrospectively registered in the Australian New Zealand Clinical Trials Registry (ANZCTR; number ACTRN: 12625000245493). The delay in study registration, which occurred after the commencement of participant enrolment, was primarily associated with the complexities of establishing a new service within a health service and its requirements; and a six week delay in early 2025 when the trial registration site was closed due to a cyber security incident. The authors confirm that all ongoing and related trials for this intervention are registered.

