
### Procedure: Interventions for carers

Interventions will be determined through shared decision-making between the carer and their primary contact CHWS staff member and will be informed by the carer-prioritised needs (CSNAT and other needs), and assessment findings. Depending on the expertise and capacity of CHWS staff, some interventions will be delivered by CHWS staff, while other interventions may require referral to other practitioners or services, within or external to Peninsula Health. Carers will be encouraged to continue other health and wellbeing strategies they may be undertaking at the time of attending the CHWS.

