**Physiotherapist**	Exercise options, including provision of (1) a tailored home exercise program; (2) a group exercise program (if CHWS physiotherapist has time capacity and relevant experience to deliver); (3) individual 1:1 physiotherapist supervised exercise program (in limited circumstances, depending on time capacity); or (4) other advice regarding maintaining/improving physical performance; Physical activity advice and support/ motivational interviewing (including opportunities for physical activity with care recipient; or independent of the care recipient); Assistance or advice regarding manual handling including for managing the care recipient, and handling of aids and equipment; • Assessment and advice regarding joint pain; • Assessment and advice regarding the need and use of mobility/gait aids (if required for the carer).	Exercise options not able to be provided through the CHWS, including referral and provision of details of a group exercise program (e.g., tai chi, hydrotherapy) not available through the CHWS physiotherapist, or when unable to attend; • Complex pain management, manual therapy, or pain management options not available through the CHWS (e.g., electrotherapy).
**Other**		**Referrals to external organisations for further assessment or interventions:** Where carers’ needs are not able to be addressed within the CHWS (e.g., outside of scope for the CHWS staff, delay in commencing intervention due to wait-list (if present)), carers will be offered referral to a suitable service or provider external to the CHWS, so that the intervention can be implemented. Examples may include referral to: a geriatrician, a general practitioner or a pharmacist for medical or medication-related issues or review; a dietitian for the management of dietary or nutritional issues; a sleep studies service for further assessment and management of sleep difficulties; or a podiatrist for management of foot pain or other foot problems.

* Data regarding these referrals will be recorded in the carers’ Electronic Medical Records and will be collected as part of the evaluation of the CHWS.

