#### Subsequent appointments and episode of care.

CHWS staff may schedule face-to-face, phone or online appointments with carers to follow up on aspects of interventions or activities after the first appointment, at a frequency that is mutually agreed upon between the carer and the staff member.

Carer involvement with the CHWS will last an average of 6 months (episode of care), from initial contact to final assessment, **with a standard episode of care being six months duration**, from the time of completion of the initial assessments. The decision regarding discharge timing will be made by the CHWS Primary contact staff member and the carer.

Although it is anticipated that the standard episode of care will be six months, carers with ongoing needs being actively addressed by the CHWS or who have added one or more extra interventions during the 6 month period may opt to continue with the Service beyond the 6 month mark. Those who complete an episode of care with the CHWS can be re-referred if their circumstances change, or new issues arise.

For situations where the person being cared for transitions from home to residential care (for permanent care, not for respite care), or in situations where a care-recipient passes away during the episode of care for the carer, the carer will have the option to continue with CHWS support (with review to determine if needs have changed), or to cease involvement with the CHWS (with re-assessment at this time point if this is acceptable to the carer).

The level of risk for adverse events associated with participating in the CHWS is considered low. If an adverse event occurs, it will be reported to the CHWS Manager, and then to the research team, who will inform the Ethics Committee. The health professional/s involved will provide or organise short term assistance and care as required, including supporting seeking medical support.

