### Data analysis

Extracted data for the CHWS evaluation comparing baseline and 6 month assessment data will be analysed using parametric analyses for continuous, normally distributed data, and non-parametric analyses for categorical or non-normally distributed data. Analyses for comparison of the continuous core and additional domain assessment between initial and 6 month assessments will be performed using generalised linear regression. Analyses will be conducted on an intention-to-treat basis.

Analysis for the cost effectiveness evaluation will involve the costing of items based on actual costs where available, and where these are not available, costs, excluding carer time, will be based on market rates, with carer time based on the minimum wage. All costs will be presented as AUD 2025/26, with costs collected prior to 2025/26 to be inflated by CPI [60]. The EQ-5D-5L raw scores will be converted to a utility index using Australian weights [61], and then into QALYs. The ICER will be calculated using the bootstrap method (5,000 replications) with the results presented on a cost-effectiveness plane and as a probability of cost-effectiveness across a range of willingness to pay thresholds (AUD $0 to $50,000) [62].

For the qualitative study (semi-structured interviews) of carers and referrers, recruitment will continue until data saturation for the carers and the referrers groups. Thematic analyses will be undertaken independently by two members of the research team for each participant group, using Braun and Clarke’s six stages of reflexive thematic analysis [63]. In cases of disagreement between the coders, the two team members will discuss their perspectives to achieve agreement on themes. The thematic analyses will then be presented to a subgroup of the research team and the CHWS staff (n = 6) to review and discuss themes, for finalisation of the thematic analysis for each participant group. A similar approach will be used for analysis of the CHWS staff interviews, although the number of interviews will be small and constrained by the number of current staff, together with interviews with any staff who leave the service. Commonalities and differences in themes between the participant groups will be identified. All quotes to support themes will be de-identified.

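### The societal cost-utility analysis costs care hours but names neither residential care nor referred services, and gives no rule for care hours after the care recipient dies or is placed

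*Protocol article*

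**What the plan says.** Item b) of Implementation (service-related) outcomes sets the frame: "A cost-utility analysis will be conducted using a societal perspective over a 12 month time horizon", made up of six months either side of the carer's first appointment. The Methods section gives the design: "A mixed methods one-group pre-post (6-month) study design will be utilised". Each carer's own earlier six months is therefore the comparator.

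The same item lists the costs: "Cost data will include CHWS intervention costs (excluding research costs); carer emergency department presentations and hospital admissions (self-report", and then the quantity of care, as "average weekly hours of care provided by the carer, by other people who are not paid, and by other people who are paid (self-report". Data analysis adds the valuation rule: "costs, excluding carer time, will be based on market rates, with carer time based on the minimum wage". The ICER is judged against AUD 50,000 per QALY.

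Three other places bear on the list:

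- Table 1 describes a health economics survey that feeds the cost-utility analysis. It collects health care utilisation, with emergency and hospital use as named components, and also the gap between preferred and actual leisure hours.
- Procedure: Interventions for carers makes referral part of what is delivered: "other interventions may require referral to other practitioners or services, within or external to Peninsula Health". The footnote to Table 2 says that data on referrals outside the service go into the carers' "Electronic Medical Records and will be collected as part of the evaluation of the CHWS".
- Subsequent appointments and episode of care provides for two events in the care recipient's course. One is permanent placement: "For situations where the person being cared for transitions from home to residential care (for permanent care, not for respite care". The other is death. After either, the carer may stay with the service, or leave with a re-assessment if willing.

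**The concern.** When a care recipient dies or is permanently placed, the hours of care given at home largely stop. Care hours are a costed item, the comparison is before against after, and there is no control group to absorb background change. A fall in hours therefore lowers the incremental cost whatever caused it. After placement, the care that replaces those hours has no named cost line. After a death nothing replaces them, but the fall is still not an effect of the service.

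Referral raises a related problem. If the service sends a carer to respite, counselling or a sleep clinic, a societal analysis should carry that cost. The article records the referrals but does not say that they are costed. Respite shows the asymmetry: it can reduce the carer's hours, which counts as a saving, while its own cost is unlisted.

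What is at stake is the comparison with the AUD 50,000 threshold. The Discussion presents sustaining the caregiving role as what is at risk when carers' health is not maintained. An analysis in which placement can make the ICER look better sits badly with that.

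**Working it through.** **Text check.**

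| Item | Named in the cost list | Elsewhere in the article |
|---|---|---|
| CHWS costs; carer emergency visits and admissions | Yes | Survey, Table 1 |
| Hours of care (carer, other unpaid, paid) | Yes | Carer time at minimum wage, Data analysis |
| Referred services | No | Part of the intervention; referral data collected for the evaluation; survey utilisation scope is open-ended |
| Residential care | No | Placement foreseen; no costing rule |
| Care hours after death or placement | No rule | Both events foreseen; analysis is by intention to treat |
| Leisure hours | Reported in addition, no money value stated | Survey information is to be used in the cost-utility analysis |

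The plan states no figure for this effect, so there is nothing to reproduce. The arithmetic below asks only whether the effect could matter.

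**Inputs, all assumed except the period and threshold.** Share of carers whose recipient dies or is placed, p = 3 to 10%. Weekly hours that stop, h = 20 to 60. Hourly value, w = AUD 20 to 25. Period after the first appointment: 26 weeks. Threshold: AUD 50,000 per QALY.

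**Apparent saving per enrolled carer** = p × h × 26 × w.

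- Low: 0.03 × 20 × 26 × 20 = AUD 312.
- Middle: 0.05 × 40 × 26 × 25 = AUD 1,300.
- High: 0.10 × 60 × 26 × 25 = AUD 3,900.

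These figures apply post-event hours to all 26 weeks. If the event falls mid-period on average and hours are averaged over the period, they halve to AUD 156, 650 and 1,950.

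**Equivalent in QALYs at the threshold**, middle case: 1,300 / 50,000 = 0.026, or 650 / 50,000 = 0.013.

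**Health gain for comparison.** Assume a utility gain of 0.03 at six months.

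- Linear rise: 0.03 × 0.5 / 2 = 0.0075 QALY, worth 0.0075 × 50,000 = AUD 375.
- Immediate rise: 0.03 × 0.5 = 0.015 QALY, worth 0.015 × 50,000 = AUD 750.

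The middle-case saving (AUD 650 to 1,300) is of the same order as the health gain being valued, or larger.

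**The opposite direction.** The Introduction says that care needs often grow over time. In the middle case, hours lost per enrolled carer are 0.05 × 40 = 2.0 per week. A mean rise of 2.0 / 0.95 = 2.1 hours per week among the other 95% would cancel the saving, and a larger rise would turn it into a net cost charged to the service.

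**The case against.** The strongest reply is that this is a condensed article and that silence is not a decision. Much of that reply stands.

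- A reader might infer that referred services are left out of the costs. The text does not establish this. The cost list is worded as what will be included, not as everything that counts. The survey's utilisation scope is open-ended, referral data are collected, and Data analysis has a general rule of actual costs, otherwise market rates. The supportable claim is that these places do not say whether referrals are costed.
- A reader might infer that death or placement is booked as a saving. No section says how hours are handled after either event, and residential care might be reported under paid hours. The saving is what follows if the list is applied as written; the plan does not state it.
- Costing residential care repairs only placement. After a death the problem is attribution in an uncontrolled comparison, and a further cost line would not change it.
- It is tempting to say that leisure hours are counted twice. Nowhere are they given a money value or added to care hours.
- It is tempting to say that the plan regards bereavement as a failure of the service. It does not; both events are handled neutrally.
- The bias need not favour the service. Care needs may rise, and a carer's EQ-5D may fall after a bereavement.

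The reply does not dispose of the point. The article itself fixes the perspective, comparator, cost items, valuation, bootstrap and threshold. A societal list that names care hours but not their main substitute is a stated choice that needs completing. The date of placement or death is also a matter of data capture, which cannot be left until analysis.

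**Conclusion.** The point holds in limited form. Under a stated societal perspective and an uncontrolled before-after comparison, the cost list counts care hours but names neither residential care nor referred services, and no rule covers hours after death or placement. As written, a fall in home-care hours can count as a saving attributed to the service, and the cost of referred services may go uncounted.

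The size cannot be determined from the documents. With assumed event rates, hours and wage, it runs from AUD 312 to 3,900 per enrolled carer, or half that for mid-period events. An assumed utility gain of 0.03 is worth AUD 375 to 750 at the threshold. So the effect could change the cost-effectiveness conclusion; the figures do not show that it will, or in which direction the net error runs. The primary effectiveness outcome is unaffected.

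**What to change.** 1. Reconcile the survey description in Table 1, the cost list in Implementation (service-related) outcomes and the footnote to Table 2. State that referred services recorded in the Electronic Medical Records are costed at market rates.
2. Cost residential care for placed recipients from the date of placement, and say that it is counted once, so that it is not also entered as paid hours.
3. Pre-specify two sensitivity analyses of the ICER: (a) without care-time costs; (b) excluding, or separately reporting, carers whose care recipient died or was placed. Analysis (b) selects on an event after baseline, so it belongs beside the intention-to-treat result and should not replace it. These two analyses, not the residential care line, address the death case.
4. State that leisure hours are not added to care hours as a cost.

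The cost is a few sentences, unit costs for referrals already recorded and for residential care, one item for the date of placement or death, and a small amount of extra analysis. The ICER may become less favourable.
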